# Clinical application of invalid foods using mealworms and evaluation of nutrition status and immune function: a study protocol for a randomized, double blind, placebo-controlled trial

**DOI:** 10.1186/s40795-019-0307-6

**Published:** 2019-11-18

**Keywords:** Nutritional balance, Malnutrition, Immune function, Invalid foods

## Abstract

**Background:**

Protein intake is important for the recovery of the immune system, physical strength, and wound healing after surgery. Sarcopenia is associated with a poor prognosis when compared to patients without sarcopenia in cancer patients. Recently, edible insects, such as mealworms, have been recognized as having a high protein content. In this study, we will evaluate the effect of nutritional status and immune function change based on a patient’s ingestion of mealworms after hepatobiliary pancreatic surgery.

**Methods/design:**

This is a prospective, two-armed, phase III study investigating the effect of mealworm improving nutrition and immune status in patients after hepatobiliary pancreatic surgery. In the trial group, the patients will be provided with mealworms for 2 months after surgery. In the control group, patients will be provided with grain powder for 2 months after surgery. The target for accrual is 168 patients. We divided in to three groups according to the type of surgery.

**Discussion:**

The primary endpoint is to evaluate body cell mass index 2 months postoperatively. Secondary endpoints include other body composition changes as well as nutrition index and immune function change. We expect that ingestion of mealworms can effectively improve the nutritional status and enhance the immune function. Mealworm can be used effectively for nutritional management of patients after surgery.

**Trial registration:**

Clinicaltrials.gov NCT03201926 Registered June 28, 2017, retrospectively registered.

## Background

Approximately 20–50% of hospitalized patients are reported to be malnourished [1]. The nutritional status of a patient generally declines during hospitalization [2, 3]. Poor food intake during hospitalization is caused by deterioration of nutritional status, and malnutrition is often associated with complications including infection, increased number of hospital days, and increased mortality [1, 4, 5]. The American Society of Parenteral and Enteral Nutrition guidelines suggests that patients at risk of malnutrition should be provided with over 80% of their calorie and protein requirements within 2 to 3 days [6]. Patients with sarcopenia imbalance generally have a lower 5-year survival rate in cancer patients [7]. The quality of protein intake is important for the recovery of the immune system, physical strength, and wound healing after surgery; this is problematic since the patient’s protein intake is generally quite poor [8].

In particular, patients who undergo a pancreatectomy or hepatectomy usually have a severe imbalance in their nutritional status due to the disruption of digestive function and nutritional absorption postoperatively. Therefore, it is necessary to use high-quality protein-derived foods that can effectively increase protein intake. The United Nations Food and Agriculture Organization (FAO) is actively encouraging food production of edible insects as a new food source for the future. Currently, various insects are used in food in many regions, including Africa, Asia, South America, and Australia. The edible insects are high in protein content (50–60%) and contain a large amount of fat, fiber, vitamins, and minerals. *Tenebrio molitor* (mealworm), which is an edible insect, contains a large amount of protein and unsaturated fatty acid. The nutritional components of these mealworm are thought to be of value as nutrient sources of high quality in a small amount of patients who need high nutrition.

The purpose of this study is to evaluate the development of long-term personalized products using mealworm and the enhancement of stability, nutritional status and immune status according to ingestion.

## Methods/design

### Study design and period

The trial is a single center, two-armed phase III study. The trial has been registered at www.clinicaltrials.gov (NCT03201926). Patients will be recruited by the Pancreatobiliary Cancer Clinic, Gangnam Severance Hospital, Yonsei University College of Medicine. The expected total duration of patient accrual is 2 years and 6 months and the follow-up period is 6 months.

### Study objectives and endpoints

The primary endpoint is to evaluate body cell mass index at 2 months postoperatively. Secondary endpoints include other body composition changes as well as nutrition index and immune function.

### Patient selection and enrollment criteria

#### Inclusion criteria

Patients scheduled for surgery with pancreatobiliary disease and liver cancer (HCC, CCC, and metastatic liver cancer)Karnofsky performance status ≥70Patients who provide informed consent

#### Exclusion criteria

Patients who underwent palliative surgeryPatients with uncontrolled preoperative conditionsPrevious history of surgery affecting nutritional status (ex, gastrectomy, colectomy, etc)Pregnant and lactating womenPatients with an allergy to mealworms

### Sample size calculation

The output of the sample size will be based on an independent two-sample t test. It is expected that there will be a difference in body cell mass between the standard meal group (control) and the group ingesting the mealworms. Assuming an alpha value of 0.05 and 1-β (power) of 0.8, 75 samples will need to be obtained for each group; considering the dropout rate of 10%, 84 samples will need to be obtained for each group. The total of the two groups is 168. The primary endpoint will be the number of subjects and body cell mass. A comparison will then be made between the two groups at 2 months. A subgroup analysis of pancreatobiliary and liver disease will also be performed as a secondary endpoint. Patients with pancreatobiliary and liver disease in our clinic have a 2:1 ratio. Therefore, the 168 patients were divided into two groups: one with 112 patients and the other with 56 patients. Patients with pancreaticobiliary disease (Group A & B) and liver (Group C) disease were assigned through stratified randomization. Pancreatobiliary disease group is divided into enteral feeding group(Group A) and non enteral feeding group.(Group B).

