#### Outcome measures

The primary outcome is the body cell mass index as measured by body composition (Inbody S-10 (Biospace, Seoul, Korea)). The secondary outcome measures are as follows: nutritional index (weight, soft lean mass, fat free mass, fat mass, PG-SGA [Scored Patient-Generated Subjective Global Assessment]) and immune function test (that assesses T cells, B cells, cytokines). We will confirm changes in immune cells through FACS (fluorescence-activated cell sorting). Based on the immune assay using blood samples from patients, we will identify changes in several cytokines.

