#### Statistical methodology

All data will be entered into a single Microsoft Excel spreadsheet with participants identified only by their unique subject number. All entries will be double-checked by another member of the research team. Statistical analysis will be performed using IBM SPSS version 21.0 (IBM Corp; released 2012. IBM SPSS Statistics for Windows Version 21.0. Armonk, NY, USA). The mean difference in nutrient intakes, changes in body measurements, changes in body composition, and PG-SGA scores will be calculated using the Wilcoxon signed rank test and the Mann Whitney test.

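### The primary endpoint is named in two incompatible ways (body cell mass index; body cell mass plus a head count), its form is unsettled, and the 80% power is not tied to the declared endpoint

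*Protocol article*

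**What the plan says.** Three places in the protocol article agree on the variable:

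- Abstract, Discussion paragraph: "The primary endpoint is to evaluate body cell mass index 2 months postoperatively".
- Study objectives and endpoints: "The primary endpoint is to evaluate body cell mass index at 2 months postoperatively".
- Outcome measures: "The primary outcome is the body cell mass index as measured by body composition". No time point is given here.

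The Sample size calculation differs. Its premise is: "It is expected that there will be a difference in body cell mass between the standard meal group (control) and the group ingesting the mealworms". It then restates the endpoint: "The primary endpoint will be the number of subjects and body cell mass". The next sentence fixes the timing: "A comparison will then be made between the two groups at 2 months".

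On the form of the variable, Study objectives and endpoints describes the secondary endpoints as the other changes in body composition, which suggests that the primary is a change too. Statistical methodology lists "changes in body measurements, changes in body composition, and PG-SGA scores" among the quantities to be tested. It names no separate analysis of a 2-month value and does not label any item as primary.

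**The concern.** A primary endpoint needs one variable, one form and one time point. Here the variable differs between sections, and the form (2-month value or change from baseline) is never chosen. Two things are at stake.

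- **Power.** The 75 per group is justified for body cell mass. A size-adjusted index need not show the same standardized difference between arms as the mass itself, and a change score has a different SD from a final value. The 80% therefore cannot be read as the power for the declared endpoint.
- **Choice after seeing the data.** Mass or index, each as value or change, makes 2 × 2 = 4 candidate primary results from the same measurements. Each could be defended by pointing to some sentence in the article. The trial is described as phase III and as retrospectively registered, so the published text is an important safeguard against such a choice.

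**Working it through.** **1. The plan's own figure.** Inputs from the Sample size calculation: independent two-sample t test, alpha 0.05 (sidedness not stated), power 0.8, 75 per group, 10% dropout.

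- Dropout step: 75 / (1 − 0.10) = 83.3, rounded up to 84 per group; 2 × 84 = 168. This reproduces the plan.
- The 75 itself cannot be reproduced forwards, because no expected difference and no SD are given for either variable. It can only be inverted.

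**2. What 75 per group detects.** From n = 2(z₁₋α/₂ + z₁₋β)² / d²:

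- Two-sided: d = (1.960 + 0.842) × √(2/75) = 0.457; with the noncentral t, 0.460.
- One-sided: d = (1.645 + 0.842) × √(2/75) = 0.406; with the noncentral t, 0.408.

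So 75 per group gives 80% power for about 0.46 SD (two-sided) of whichever variable is tested. What may differ between mass and index is the effect to be expected, in SD units.

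**3. Mass against index.** The article gives nothing to convert one into the other, so this is illustration only. Suppose the standardized effect on the index is a multiple of 0.46 (assumed multiples; two-sided t test, 75 per group):

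| Multiple | Power |
|---|---|
| 0.8 | 61% |
| 0.9 | 71% |
| 1.0 | 80% |
| 1.1 | 87% |
| 1.2 | 92% |

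**4. Value against change.** Assume equal SDs before surgery and at day 60, with baseline correlation r. Then SD(change) = SD × √(2(1 − r)), and the standardized effect on change is 0.46 / √(2(1 − r)). A comparison of day-60 values adjusted for baseline has residual SD of SD × √(1 − r²). Power of a two-sided t test with 75 per group:

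| r (assumed) | 2-month value | Change | Adjusted for baseline |
|---|---|---|---|
| 0.3 | 80% | 66% | 84% |
| 0.5 | 80% | 80% | 90% |
| 0.7 | 80% | 95% | 98% |

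The form of the variable alone moves power from 66% to 98% in this range. This step concerns value against change; it says nothing about mass against index.

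**5. False positives from choosing.** Under no true effect, the correlation between the 2-month value and the change is √((1 − r)/2), which is 0.59 at r = 0.3 and 0.32 at r = 0.8. Both outcomes were simulated with 75 per arm and a t test on each, and success was claimed if either gave p < 0.05. The false-positive rate was about 9% across r from 0.3 to 0.8. For comparison, two independent tests would give 1 − 0.95² = 9.75%.

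**The case against.** The strongest defence is that three statements agree on the index, two of them with the 2-month time point. The outlier is one badly worded section, where body cell mass may simply be shorthand for the index. The dropout arithmetic is right, and an article may leave the form of the analysis to a full protocol or SAP that is not shown.

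Much of this stands. Shorthand is possible, and the point does not show that the sample size is wrong. Silence on value or change would be no finding by itself. But the Sample size calculation does more than stay silent: it makes its own explicit statement of the primary endpoint, which conflicts with the others and contains an item that is not an outcome. It gives no difference or SD from which a reader could confirm the shorthand. On the form, the sections point in different directions.

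Several stronger readings are tempting but not supported:

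- **The endpoint is stated three ways.** Statistical methodology does not call change in body composition primary. There are two named versions and an unsettled form.
- **Four primary endpoints are declared.** The four results are candidates that the text leaves open.
- **Type I error has a ceiling of 9.75% for two versions, or 1 − 0.95⁴ = 18.5% for four.** These are figures under independence; the general upper bounds are 2 × 5% = 10% and 4 × 5% = 20%. The four versions are correlated, and mass and index may be strongly so.
- **168 patients is too few.** With no difference or SD for the index, this can be neither shown nor excluded.

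**Conclusion.** The point holds as an inconsistency in the text that has to be resolved before analysis. The declared primary variable (the index) is not the variable named in the power calculation (body cell mass, with a number of subjects attached), and the form is not settled between 2-month value and change.

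Its size: choosing the better of value and change alone raises the false-positive rate from 5% to about 9%. No figure is offered for the choice between mass and index, because the article does not allow one. The power for the declared endpoint is unknown; if its standardized effect were 0.8 to 1.2 times the implied 0.46, power would run from 61% to 92%. These results rest on assumptions that the article does not state: a two-sided 5% test, equal SDs at both times, and baseline correlations of 0.3 to 0.8 for the false-positive rate and 0.3 to 0.7 for the power table.

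**What to change.** 1. In the Sample size calculation, replace the sentence that restates the endpoint with: *The primary endpoint is body cell mass index at 2 months (postoperative day 60).* Delete the reference to the number of subjects.
2. In the same section, restate the basis for body cell mass index, with the expected difference and SD that were used. Add that 75 per arm gives 80% power for about 0.46 SD if the test is two-sided at 5% (0.41 SD if one-sided), and say which applies. The 0.46 describes what the number detects; it does not replace the expected difference and SD.
3. In Outcome measures, add the time point.
4. In Statistical methodology, name the primary analysis: between-arm comparison of day-60 body cell mass index, adjusted for the pre-operative value. The conflict itself does not require the adjustment, but it settles value against change and raises power under the assumptions above. Table 4 appears to schedule the pre-operative measurement already, although its layout is broken in the text at hand.
5. List body cell mass in kg and change from baseline as secondary or sensitivity results.

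The cost is wording and a slightly different primary analysis, with no new measurements or patients. If the expected difference and SD turn out to have been for mass rather than the index, the sponsor should check the 75 per arm against figures for the index.

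### The disease subgroup analysis is a secondary endpoint, but the tests named for body composition cannot show whether the arm effect differs between pancreatobiliary and liver patients

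*Protocol article*

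**What the plan says.** Under Sample size calculation the protocol article announces the analysis: "A subgroup analysis of pancreatobiliary and liver disease will also be performed as a secondary endpoint". The same section expects a 2:1 ratio of pancreatobiliary to liver disease, splits the 168 patients accordingly ("one with 112 patients and the other with 56 patients"), and makes disease group the factor for stratified randomisation. It gives no method for the subgroup analysis.

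Statistical methodology is the only section on analysis. It says that differences in nutrient intakes and PG-SGA scores, and changes in body measurements and body composition, "will be calculated using the Wilcoxon signed rank test and the Mann Whitney test". The primary outcome, body cell mass index, is a body composition measure (Outcome measures). The sample size rests on a different test: "The output of the sample size will be based on an independent two-sample t test". Table 4 shows body composition measured before surgery and at Day 60.

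**The concern.** The disease comparison is built into the design: it is a named secondary endpoint, has planned stratum sizes and is the stratification factor. The question such an analysis invites is whether the supplement works differently in the two diseases. The signed rank test compares paired values. The Mann Whitney test compares two independent groups, here the arms. Neither contrasts the arm effect in one disease with the arm effect in the other.

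If only these tests are used, the natural output is one between-arm p-value per disease. Reading one significant and one non-significant result as evidence of a different effect is a known error. Here it could become a statement about who benefits, and readers would find it believable because the strata also differ in type of surgery and, for Group A, in feeding route.

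**Working it through.** **Inputs**
- Alpha 0.05, power 0.80, 75 evaluable per arm, independent two-sample t test, 10% dropout, 112 and 56 patients by disease (all from Sample size calculation).
- 1:1 allocation (Randomization), taken to hold within each stratum.
- Assumptions: two-sided alpha (the protocol does not say), the same dropout in both strata, the same true effect in both diseases.
- Effect size: not stated, so back-solved below.

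**1. The plan's own figure.** 75 / (1 − 0.10) = 83.3, rounded up to 84 per arm, 168 in total. This reproduces.

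**2. Implied effect.** Normal approximation: d = (1.960 + 0.842) × √(2/75) = 0.457 SD. Exact t test: d = 0.460 SD. If the design was one-sided, d = 0.408 SD.

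**3. Evaluable patients per arm.** Pancreatobiliary: 112 × 0.9 / 2 ≈ 50. Liver: 56 × 0.9 / 2 ≈ 25.

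**4. Power in each stratum at 0.46 SD (t test).** p₁ = 0.625 for pancreatobiliary, p₂ = 0.358 for liver.

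**5. Pattern of results when the effect is identical in both.**
- Pancreatobiliary only: p₁(1 − p₂) = 0.625 × 0.642 = 0.40
- Liver only: p₂(1 − p₁) = 0.358 × 0.375 = 0.13
- Exactly one significant: 0.54 (0.536 before rounding)
- Both significant: 0.625 × 0.358 = 0.22
- Neither: 0.375 × 0.642 = 0.24

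A simulation of 20,000 trials with the Mann Whitney test itself gave 0.535 for exactly one significant. With no dropout (56 and 28 per arm) the t-test figure is 0.537.

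**6. Dependence on the assumed effect (t test, 50 and 25 per arm).**

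| Common effect (SD) | Exactly one significant |
|---|---|
| 0.2 | 0.24 |
| 0.3 | 0.38 |
| 0.4 | 0.50 |
| 0.46 | 0.54 |
| 0.6 | 0.47 |
| 0.8 | 0.22 |

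The figure exceeds one half only between about 0.40 and 0.56 SD (0.41 to 0.57 SD for Mann Whitney). At the one-sided 0.408 SD, two-sided subgroup tests give 0.50 to 0.53.

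**7. What drives it (at 0.46 SD).** With equal strata of 37.5 per arm, exactly one is significant with probability 2 × 0.503 × 0.497 = 0.50. With the same 2:1 split but 200 and 100 per arm it is 0.10. Low power is therefore the main cause. The split adds about 4 percentage points and tilts the result: 0.40 pancreatobiliary only against 0.13 liver only, instead of 0.25 each.

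**8. The alternative.** An interaction test at the 5% level would signal a false difference 5% of the time. Its standard error in SD units, before any gain from baseline adjustment, is √(2/50 + 2/25) = 0.346. Its power for an interaction of 0.457 SD is Φ(0.457/0.346 − 1.96) = 0.26. With 56 and 28 per arm the standard error is 0.327 and the power 0.29.

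**The case against.** The strongest reply is that a condensed article need not say how a secondary subgroup analysis is modelled, and an analysis plan that is not shown may contain an interaction term. That is fair, and silence alone would be no finding. But the article is not silent: it names the tests for body composition, and those tests cannot answer the question that its own secondary endpoint raises.

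Several stronger readings are tempting and are not supported:
- **That the plan will contrast p-values between diseases.** Nothing says so. Statistical methodology does not assign its tests to the subgroup analysis, and reporting the arm difference within each stratum is legitimate. The harm is conditional.
- **That only rank tests are in play.** Sample size calculation names a t test, though for sizing, and Mann Whitney is itself a between-arm test. A t test run within each stratum would have the same limitation.
- **That an identical effect would more often than not look like a difference.** This holds only for a common effect of roughly 0.40 to 0.57 SD, which the protocol never states.
- **That the 2:1 split alone produces the pattern.** Step 7 shows that low power does most of the work.
- **That a pancreatobiliary-only result is to be expected.** Its probability is about 0.40 at the back-solved effect.

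It can also be said that the interaction test gains little, with power of only 0.26 to 0.29. That stands as a limit on what the trial can learn. It is no reason to infer a difference from two separate p-values.

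**Conclusion.** The point holds in a limited form. The named secondary endpoint and the named tests do not match, because neither test can estimate or test a difference in arm effect between diseases. If the strata are tested separately and compared by significance, a common effect of 0.46 SD yields a misleading split about 54% of the time, against 5% for an interaction test. Over common effects of 0.2 to 0.8 SD the range is about 22% to 54%, so the problem does not depend on passing one half.

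The figures rest on the back-solved effect, two-sided 5% tests, equal dropout in the strata and 1:1 allocation within them. Severity is low: the analysis is secondary, no subgroup power is claimed, and the primary comparison is unaffected.

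**What to change.** For the subgroup analysis, fit one model to all evaluable patients: Day-60 body cell mass index on arm, baseline value, disease stratum and arm-by-stratum. Report each stratum's adjusted arm difference with its 95% confidence interval. State that any claim of differing effects rests on the interaction estimate and its interval only, and label it exploratory. If an unseen analysis plan already does this, a sentence in the protocol pointing to it is enough.

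The cost is one additional model and a few lines of text. No new data are needed, since the stratum is known at randomisation and baseline body composition is already in Table 4. It does put a linear model in place of the named rank tests for this analysis, which should be said openly. The other downside is imprecision: with power of about 0.26 to 0.29 for an interaction as large as the design effect, a wide interval must not be read as proof that the effects are equal.
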